## Abstract

**Background:**

Coronary heart disease (CHD) has become one of the biggest health problems in the world. Stable angina is a common clinical type of CHD with poor prognosis and high mortality. Although there are various interventions for stable angina, none of them can significantly reduce mortality. Both basic and clinical research have shown that Suxiao Jiuxin Pill (SJP) can relieve the symptoms of angina pectoris and improve the clinical efficacy, but there is a lack of high-quality clinical research to provide research-based evidence. We design a randomized, double-blind, placebo-controlled trial to evaluate the efficacy of SJP for stable angina.

**Methods/design:**

This is a prospective, randomized, double-blind, placebo-controlled, and multicenter trial. The trial will enroll 324 participants with chronic stable angina (Qi Stagnation and Blood Stasis syndrome). All participants will have received the conventional therapy of chronic stable angina. Participants will be randomized into two groups, conventional therapy plus SJP group and conventional therapy plus placebo group. Eligible participants will receive either SJP or placebo (five pills administered orally, three times daily) in addition to conventional treatment for 24 weeks. The primary outcomes are the symptom improvement rate of angina from baseline to 4 weeks after inclusion and major adverse cardiovascular events (MACE). The secondary outcomes are angina classification (CCS), improvement of traditional Chinese medicine (TCM) syndromes, Seattle Angina Scale score, the dosage of emergency drugs and the stopping rate, and electrocardiogram (EKG) efficacy. Adverse events will be monitored throughout the trial.

**Discussion:**

Integrated traditional Chinese and Western Medicine is commonly used for angina in China. This study will evaluate the clinical effectiveness and safety of SJP for angina. The results of the trial will provide high-level clinical research-based evidence for the application of SJP instable angina.

**Trial registration:**

This study protocol was registered on 14 March 2019. The registration number is ChiCTR1900021876 on the Chinese Clinical Trial Registry.

**Supplementary Information:**

The online version contains supplementary material available at 10.1186/s13063-021-05448-6.

## Administrative information

Note: the numbers in curly brackets in this protocol refer to Additional file 1: SPIRIT checklist item numbers. The order of the items has been modified to group similar items (see http://www.equator-network.org/reporting-guidelines/spirit-2013-statement-defining-standard-protocol-items-for-clinical-trials/).

## Background

Coronary heart disease (CHD) stable angina pectoris is also known as stable labor angina pectoris, which refers to the clinical syndrome caused by myocardial ischemia and hypoxia due to coronary atherosclerotic stenosis or thrombosis and spasm. Specifically, it is defined such that its clinical manifestations are relatively stable within 1 to 3 months, i.e., the number of daily and weekly pain episodes is approximately the same, the degree of labor and emotional agitation to induce pain are the same, the nature and location of pain do not change during each episode, and the pain duration is similar. It has characteristics, such as high mortality and many complications. The prevalence and mortality of cardiovascular disease (CVD) in China are continuously rising [1]. The prevalence of angina pectoris in China is 3.6% [2]. In the USA, about 10 million people suffer from angina pectoris and more than 500,000 new cases are diagnosed each year [3]. The annual mortality rate of stable angina is as high as 3.2% in Europe [4]. The aims of treatment for angina include controlling the clinical symptoms and preventing cardiovascular events. Western medicine treatments include antiplatelet therapy (APT), angiotensin-converting enzyme inhibitor (ACEI) or angiotensin II receptor antagonist (ARB), beta-blockers, calcium channel blockers, nitrate, and statins [5]. However, many participants continue to suffer from angina. Angina worsening and repeated hospitalization has caused severe economic burden on families and society. Supplementary replacement therapy is necessary for the treatment of angina. Integrated traditional Chinese and Western Medicine is commonly used for angina in China.

Suxiao Jiuxin Pill (SJP, produced by Tianjin Zhongxin Pharmaceutical Group Co, Ltd.) is a patented drug made of active ingredients from Chuanxiong and Borneol, and it has the effect of regulating Qi and promoting blood circulation. SJP can increase coronary blood flow, improve myocardial cell hypoxia, and relieve angina pectoris similar to nitroglycerin [6, 7]. SJP has been commonly used in the treatment of angina pectoris with integrated Chinese and Western medicine, and these participants have also been diagnosed with Qi stagnation and blood stasis syndrome [8–10]. Experimental research has confirmed that SJP could dilate the blood vessels by regulating [Ca2+], increase myocardial blood supply, and promote cardiomyocyte proliferation in vitro and in vivo [11, 12]. Several clinical researches on SJP have confirmed its efficacy in mitigating the symptoms of angina without any serious side effects [13, 14]. However, the evidence remains weak due to the poor methodological quality of included studies [7]. The purpose of this study is to clarify the efficacy and safety of SJP in the treatment of angina pectoris through a high-quality clinical experimental design. The experimental results will provide high-level research-based evidence for the clinical application of SJP.

## Methods/design

### Study objectives

To evaluate the effectiveness and safety of SJP in patients with chronic stable angina pectoris (Qi stagnation and blood stasis syndrome) based on standardized western treatment.

### Study design

The study is designed as a randomized, double-blind, multicenter, placebo-controlled trial. To avoid regional differences, the study will be conducted in 11 hospitals from different regions of China. Data management and statistical analysis will be performed by the statistical department in China Evidence-based Medicine Center, West China Hospital, Sichuan University. This study will be conducted by following the Declaration of Helsinki and the guidelines of Good Clinical Practice (GCP). The study has also been approved by the ethics committee in Shuguang Hospital (Ethics approval number: 2019-649-04-01). Trial registration: ChiCTR, ChiCTR1800014258. Registered on 13 March 2019 at chictr.org.cn (http://www.chictr.org.cn/showproj.aspx?proj=34955). Before randomization, all participants in this study must sign an informed consent form.

The participants who fulfill both the inclusion and exclusion criteria will be recruited into the study. Participants sign consent form. Demographic information (including date of birth, gender, ethnicity, height, and weight), medical and treatment history (including course of disease, smoking, drinking history), angina pectoris score, Seattle angina pectoris scale score, physical and chemical examinations (EKG, blood lipids, C-reactive protein, tumor necrosis factor alpha, and interleukin 6) and scores from the four traditional Chinese medicine (TCM) diagnostic methods are collected. The study design is shown in Fig. 1.

**Fig. 1 Fig1:**
[figure not shown]
Flow diagram

### Eligibility criteria

Eligible patients will be those who fulfill all of the following inclusion criteria and who do not have any of the listed exclusion criteria.

#### Diagnostic criteria

Basis of diagnosis of CHD (diagnosis of any of the following)/The diagnostic criteria for CHD will be ① history of myocardial infarction (MI); ② coronary angiography or computed tomography coronary angiography confirmation of stenosis greater than 50%; and ③ noninvasive imaging stress test diagnostic of coronary artery disease (CAD) (e.g., positive treadmill exercise test (male only), nuclear perfusion scan). Patients will be considered to be diagnosed with CHD if they meet at least one of these criteria [4, 5, 15].The angina pectoris severity classification diagnostic criteria were formulated by following the “ACC/AHA /ACP-ASIM Chronic Stable Angina Pectoris Management Guidelines”. Canadian Cardiovascular Society (CCS) Angina Pectoris Severity Classification [16].

#### The standardization of TCM

According to the Expert Consensus for Diagnosis and Treatment of Coronary Heart Disease with Stable Angina Pectoris (2018) [17], doctors choose medications based on standardized western medications. The technical guidelines for clinical research of TCM drugs and natural drugs used for angina and coronary artery disease (2011) describe the main symptom as chest pain (chest tightness) [18]. The secondary symptoms are sighing and bloating. Tongue characteristic is a purplish tongue and pulse manifestation is a string or astringent pulse. A patient must have the main symptom and one of the secondary symptoms, in accordance with the tongue and pulse conditions, to be diagnosed with Qi stagnation and blood stasis syndrome [19].

#### Inclusion criteria

Age 18 to 80 years;Diagnosed with CHD;CCS classification of angina grades I–III;Patients with angina pectoris twice or more per week;TCM diagnosis of Qi stagnation and blood stasis syndrome; andSubmitted informed consent.

#### Exclusion criteria

Myocardial infarction in the past 3 months and moderate to severe heart failure, severe cardiopulmonary insufficiency;Percutaneous coronary intervention or coronary artery bypass grafting or implantation of a pacemaker in the past 3 months;Uncontrolled hypertension with systolic blood pressure (SBP) ≥ 180 mmHg or diastolic blood pressure (DBP) ≥ 100 mmHg, or severe arrhythmia;Chest pain caused by other diseases, such as psychosis, severe neurosis, hyperthyroidism, biliary heart syndrome, gastroesophageal reflux, and aortic dissection;Alanine transaminase and/or aspartate transaminase values two times higher than the upper reference limit value. Renal insufficiency (defined as serum creatinine value one and a half times higher than the upper reference limit value). Other severe primary diseases, such as hematopoietic system disease and malignant tumor;Allergy to the ingredients of the study drug; andParticipation in other clinical trials in the past 1 month.

### Randomization

Eligible patients will be randomly assigned to the treatment group or the control group in a 1:1 ratio, using SAS 9.4 statistical software and a block randomization schedule. The size of the blocks is four. Randomization of the trial participants will be completed in an independent data center. Each participating hospital will have an independent drug administrator responsible for random coding and drug management. Each center set up an independent drug administrator, who was responsible for random coding and drug management.

### Blinding

Blind editing and blind bottom preservation: All patients and researchers will be blinded to the treatment assignments until the study is completed. Personnel unrelated to this clinical trial will complete the preparation of drug blinding and emergency letters. Duplicate blinding codes will be kept in the clinical research institution of drugs at Shuguang Hospital. The blinding codes will not be broken until all clinical data are entered into a database and locked, except in an emergency situation.

In this study, the data security monitoring committee decided whether the subjects who had security incidents needed to conduct emergency unblinding or discontinue the study. During the study period, once a safety event occurred to the participants, the preliminary assessment was conducted by the researchers, and the data security monitoring committee held a safety event assessment summary meeting every six months. The data management was performed by the third party certified by relevant departments, and the data acquisition and management were implemented by the validated EDC system.

### Interventions

Eligible patients will be randomized to either the treatment group or the control group. Based on the guidelines for diagnosis and treatment of chronic stability angina in China (2018) [5], doctors will give routine treatment. Both the experimental group and control group can take antiplatelet drugs, angiotensin-converting enzyme inhibitor (ACEI) or angiotensin II receptor antagonist (ARB), statins, calcium ions antagonists, beta-blockers, and long-acting nitrates; the above drugs can continue to be used without changing the original dose; nitroglycerin 0.5 mg can be taken sublingually when angina pectoris is intolerable; and detailed records of the frequency and the amount of medication. Other oral or intravenous traditional Chinese medicines that might potentially interfere with the therapeutic effects of SJP will not be allowed.

During the treatment period, eligible patients will be given SJP or placebo pills and they will have to take 5 pills of the study medication three times daily. SJP is composed of tetramethylpyrazine and borneol approval number Z12020025 of the China State Food and Drug Administration [SFDA]). The SJP and placebo pills are provided by Tianjin Zhongxin Pharmaceutical Group Co., Ltd. (Tianjin, China). The placebo pills are similar to the SJP, with a comparable appearance. Each pill weighs 40 mg. The primary ingredient of the placebo pills is starch. By adding flavoring agents and food colorants, the placebo pills achieve a texture, smell, color, and taste comparable to the contents of the SJP.

### Outcomes

The primary outcome is the effect in angina pectoris, a composite endpoint of cardiovascular events (cardiac death, nonfatal myocardial infarction, revascularization with PCI or coronary artery bypass graft, heart failure, and hospitalization for coronary heart disease). The secondary outcomes are angina classification, improvement of TCM syndromes, Seattle Angina Scale score, the dosage of emergency drugs and the stopping rate, EKG efficacy, and scores of the four TCM diagnostic methods.

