### Sample size

The sample size will be calculated based on a 10% increase in effective treatment after treatment. It was hypothesized that the effective treatment rate for patients receiving standard western medicine treatment is 83% and that for patients receiving both traditional Chinese medicine and western medicine treatment is 93%. The participants will be arranged into the treatment or control group in a ratio of 1:1. According to the one-tailed difference test formula, there should be 162 participants in each group (significance level α is 0.05 and power (1-β) is 0.80 in the one-sided test) and the incomplete rate should be less than 20%. A total of 324 participants will be included.

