### Statistical approach

Efficacy will be determined by the full analysis set (FAS) and per protocol set (PPS), while the safety assessment will be based on the safety set (SS). The statistical evaluation of FAS will follow the principle of intention to treat (ITT). For the missing values of the main efficacy evaluation indicators, the method of the last observation carried forward (LOCF) will be used. Continuous variables were shown as mean ± standard deviation (SD) and were compared using the *t* test or the nonpara-metric Mann-Whitney *U* test, as appropriate. The count variables were shown as the number of cases and percentage, and the chi-square test was used for comparative analysis. The symptom improvement rate of angina is to calculate the total score of angina pectoris according to the degree of pain, the number of attacks, and the duration. The total score is effective when it is lower than or equal to 30% of the baseline, and invalid when it is less than 30%. The symptom improvement rate of angina was analyzed by chi-square test. The participants who had any cardiovascular event during 24 weeks of treatment will be identified as the occurrence of cardiovascular events. The RR and 95% confidence interval of the two groups were calculated by logistic regression model. Statistical analysis will be performed using SAS 9.4 software.

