Several clinical studies on SJP have confirmed its efficacy in mitigating the symptoms of angina without any serious side effects. A systematic review including 41 trials involving 6276 participants was included in the analysis. A meta-analysis of the clinical efficacy of the results. The analysis showed that SJP can effectively reduce the lipid profile and improve the hemorheology index in patients with CHD. This is due to the effects of its ingredients (borneol and L. chuanxiong), which may improve coronary artery circulation and ECG results. Based on the Jadad score, most of the clinical studies included in the meta-analysis were of poor quality. Only a few studies reported a detailed research methodology [13]. Therefore, it is necessary to scientifically design high-quality, large-scale, clinically proven therapeutic effects of fast-acting Jiuxin pills on angina. Evaluation of the therapeutic effect on cardiovascular disease includes improvement of clinical symptoms and long-term prognosis of the disease. Therefore, in addition to the efficacy in angina pectoris, the main therapeutic index of this experiment also observed the composite endpoint of cardiovascular events (MACE). The medical model has currently changed to the “biological-psycho-social” model [23]; people are no longer satisfied with simple life extension, but they have a higher hope for the quality of life. Therefore, the secondary efficacy in our study design, the indicators, mainly observe the improvement of patients’ symptoms and quality of life, including the secondary outcomes, such as angina classification (CCS), TCM syndromes, and Seattle Angina Scale score (SAQ) [24].

Our clinical design plan is based on the principles of international clinical trials. Strict quality control measures are designed using double-blind, randomized, placebo-controlled, multi-center research methods. A professional independent statistical group is responsible for statistical analysis and reporting, and it will analyze the combined data from all research centers. Strict trial design and supervision during the trial implementation process will ensure a scientific and objective evaluation of the efficacy and safety of SJP in the treatment of angina pectoris.

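### Outcomes merges the angina effect and the cardiovascular composite into one undated primary, while other sections treat them as two; the sample size provides alpha and power for the symptom rate only

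*Protocol article*

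**What the plan says.** The sections of the protocol article describe the primary outcome differently.

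- **Outcomes:** "The primary outcome is the effect in angina pectoris, a composite endpoint of cardiovascular events", followed by a list of event types. The verb is singular, the angina effect is described as if it were the composite, and no time point is given.
- **Abstract, Methods/design:** "The primary outcomes are the symptom improvement rate of angina from baseline to 4 weeks after inclusion and major adverse cardiovascular events (MACE"). Two outcomes, with symptoms at week 4.
- **Discussion:** besides angina efficacy, "the main therapeutic index of this experiment also observed the composite endpoint of cardiovascular events (MACE"). Again two.
- **Statistical approach:** the two are analysed separately, with a chi-square test for the symptom responder rate and a logistic model giving an RR with a 95% interval for events during 24 weeks of treatment. No visit is named for the symptom rate, and no level or sidedness is given for either analysis. On analysis sets: "Efficacy will be determined by the full analysis set (FAS) and per protocol set (PPS").
- **Sample size:** "The sample size will be calculated based on a 10% increase in effective treatment after treatment". The assumed rate under "standard western medicine treatment is 83% and that for patients receiving both traditional Chinese medicine and western medicine treatment is 93"%, with "significance level α is 0.05 and power (1-β) is 0.80 in the one-sided test". This gives 162 per group and 324 in total, with an incomplete rate below 20%. MACE is not mentioned.

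**The concern.** Outcomes is the section a reader would consult to learn what the trial's main conclusion rests on, and as printed it does not agree with the rest of the article. Read literally, it makes the event composite the sole primary, which the trial was not sized for. Read with the abstract, there are two primaries, of which one takes the whole stated alpha and all 324 participants.

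Two things follow. If success on either outcome were enough, the overall chance of a false claim could exceed the stated 5%. And a null MACE result could be reported as a failed primary when the trial had little chance of detecting a realistic effect on it. The symptom time point matters too: hospital visits are scheduled at weeks 4, 12 and 24, and only the abstract says which one counts.

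**Working it through.** **1. Reproduce the plan's sample size.** Inputs from the Sample size section: rates 0.83 and 0.93, one-sided α = 0.05 (z = 1.645), power 0.80 (z = 0.842), 1:1 allocation, 20% incomplete.

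n = [1.645·√(2·0.88·0.12) + 0.842·√(0.83·0.17 + 0.93·0.07)]² / 0.10²
= [1.645·0.4596 + 0.842·0.4541]² / 0.01 ≈ 129.5, so 130 evaluable per arm.

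Allowing for 20% incomplete: 129.5/0.8 ≈ 161.9, which rounds up to 162 (163 if 130 is divided by 0.8). The stated 162 reproduces, with the full one-sided 0.05 spent on the symptom rate.

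**2. Error across two outcomes, if either may be claimed and neither has a true effect.**

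| Reading | Calculation | Result |
|---|---|---|
| Both at one-sided 0.05, independent | 1 − 0.95² | 9.75% |
| Same, correlation 0.3 | bivariate normal | 9.3% |
| Same, correlation 0.5 | bivariate normal | 8.8% |
| Same, correlation 0.8 | bivariate normal | 7.5% |
| Symptoms one-sided 0.05; MACE by its 95% interval (0.025 in the direction of benefit), independent | 1 − 0.95·0.975 | 7.4% |
| Both two-sided 0.05, false benefit only, independent | 1 − 0.975² | 4.9% |
| Both outcomes must succeed | – | no inflation |

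**3. MACE power.** The article gives no MACE rate and no target effect, so the control rates and risk ratios here are assumptions. With n = 162 per arm, one-sided 0.05, control rate p₁, p₂ = RR·p₁ and p̄ their mean:

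power = Φ{ [(p₁ − p₂)√n − 1.645√(2p̄(1 − p̄))] / √(p₁(1 − p₁) + p₂(1 − p₂)) }

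| Control rate | RR 0.70 | RR 0.50 |
|---|---|---|
| 5% | 16% | 32% |
| 10% | 25% | 53% |
| 20% | 42% | 81% |

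These assume that all 162 per arm are evaluable. With 130, the RR 0.70 figures become 15%, 22% and 36%, and the best case (20%, RR 0.50) falls from 81% to 73%.

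**4. What each way of controlling error does to the stated 80% power.**

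- *Split alpha, one-sided 0.025 each:* the error is 1 − 0.975² = 4.9%, but symptoms then need 165 evaluable per arm, or 165/0.8 → 207 per arm and 414 in total. At the planned size, symptom power falls from 80.1% to 70.1% with 130 evaluable (79.4% if all 162 are).
- *Require both:* no inflation, but success then depends on the MACE power in step 3.
- *Fixed sequence, symptoms first:* the symptom test keeps the full alpha and its 80% power, and no participants are added.

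**The case against.** The sentence in Outcomes has most likely lost an 'and'. The abstract, Statistical approach and Discussion agree on two outcomes, so the contradiction can be seen as a drafting slip. A success rule, a multiplicity procedure and the ranking of analysis sets are commonly left to an analysis plan, which is not shown here. Both arguments have force. What stands against them is that the defining section is wrong as printed, and that the article itself commits all of its stated alpha and sample size to one of the two outcomes. A later split of alpha could not restore the lost symptom power without more participants.

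A reader might infer three stronger claims, which the article does not support.

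- *That the trial runs at about twice its stated error.* The one-sided 0.05 appears only in the sample size calculation. Statistical approach gives no test level, MACE is given an interval with no success criterion, and nowhere is either outcome alone said to suffice. The 9.75% is one scenario at the upper end of the range above.
- *That MACE cannot support a primary conclusion at this size.* With a 20% control rate and a halving of risk, power is 81%. The 3.2% annual mortality in Background does not settle the matter, because it is a European upper figure for death and the composite also counts infarction, revascularization, heart failure and hospitalization.
- *That naming both FAS and PPS opens a further route to a false claim.* Reporting both is ordinary, the FAS is tied to intention to treat, and nothing says that success in the PPS alone would count.

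Nor does the point require MACE to lose its primary label. The Discussion gives a reason for including it: treatment should be judged on prognosis as well as symptoms.

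**Conclusion.** The point holds as a contradiction between sections and a badly fixed primary outcome. Outcomes must be reconciled with the abstract, Statistical approach and Discussion, and the week 4 time point must appear in the body of the article. The sample size supports the symptom rate only.

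The effect on error is conditional. It is 9.75% if either outcome suffices, both are tested at one-sided 0.05, they are independent and neither has a true effect. It is lower under positive correlation or stricter test levels, and absent if both are required. MACE power is probably low, but that judgement rests on assumed control rates of 5% to 20% and risk ratios of 0.70 and 0.50, since the article supplies neither.

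**What to change.** Before unblinding:

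1. Rewrite Outcomes to name two separate outcomes, the symptom effective rate at week 4 and MACE through 24 weeks, and make the abstract, Outcomes and Statistical approach agree.
2. Test them in fixed sequence in the FAS: the symptom rate first at the full alpha, then MACE only if the first succeeds. Otherwise report MACE as an estimate with its interval.
3. State that the sample size and 80% power apply to the symptom rate only.
4. Treat the PPS as supportive.

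Whether MACE keeps a primary label is the sponsor's choice; the sequence controls the error either way.

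The cost is a protocol amendment, which Data management and quality control says must be reapproved by the ethics committee, and giving up any confirmatory MACE claim if the symptom test fails. No participants are added and the stated symptom power is kept. Trial status reports 293 of the 324 already recruited, but the Blinding section keeps the codes sealed until database lock except in an emergency, so the change can still be made blind if it is made before then.
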